**Ethics and dissemination:**

This study received ethical approval from the University College London research ethics committee (3352/001) and from the bioethics committee of the Odontology Faculty at the University of Antioquia (CONCEPTO 01–2013). Findings will be disseminated to commissioners, clinicians and service users via papers and presentations at international conferences.

Strengths and limitations of this studyWe propose a genome-wide association study of both baseline pain sensitivity as well as nociceptive sensitisation.The study will be conducted in an admixed population in Colombia, with variable proportions of European, Native American and sub-Saharan African ancestry.Phenotypic data will be collected by a single trained examiner, thus producing high-quality measures.Because we are focusing on highly reproducible pain phenotypes obtained at a single centre, our initial sample size is limited to 1500–2000 participants. This will allow us to identify only genetic variants that have intermediate and large (but not small) effect sizes.

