### Mustard oil evoked nociceptive sensitisation

After the baseline sensory measures, an acetate template will be used to mark a star with eight spokes each containing eight points at 1 cm increments on the volar forearm (figure 2). The skin temperature will be standardised by placing the 32°C warm thermode over the center of the star for 5 min before starting. We will then apply a sensitisation paradigm using mustard oil (AITC (Sigma), diluted at 30% in olive oil) as previously performed.^36^ AITC, the active component of mustard oil, activates the ion channel TRPA1 and evokes skin flare and nociceptive sensitisation.^37^ A small cotton swab soaked in mustard oil will be applied to a 0.64 cm^2^ area on the volar forearm and held in place with a Tegaderm (3M) for 10 min.^36^ During this time, pain scores will be recorded every 30 s using an electronic VAS ranging from 0 to 100. After 10 min, the mustard oil will be removed and the area of the skin flare will be recorded to the nearest 0.5 cm at each spoke.^7^ Eight triangular shapes will be created by joining the points on adjacent spokes and the total area will be calculated by adding all triangular segments. The area of mustard oil application will be subtracted from the total area to determine the area of secondary flare (flare area).

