**Figure 2 F2:**
[figure not shown]
Method to determine area of flare, punctuate hyperalgesia and allodynia. (A) An acetate template is used to mark a star with eight spokes containing eight points at 1 cm increments on the volar forearm. (B) A small cotton swab soaked in 30% mustard oil is applied in the center of the star and (C) held in place with a Tegaderm for 10 min. During this time, pain scores are recorded every 30 s. (D and E) After removal of the mustard oil, the skin flare will be marked and the area calculated. (F) The area of brush-evoked and punctuate hypersensitivity will be determined with a brush and a 98.1 mN von Frey hair respectively (pictured) by testing potential hypersensitivity at each point on the eight spokes.

After mapping of the flare, the area of brush-evoked hypersensitivity will be determined with a brush (Nr 5 Senselab, Somedic, Sweden) by applying 1 cm long strokes at each of the points on the eight spokes, starting from the outside and moving towards the sensitised centre. The area of punctuate hypersensitivity will be determined with a 98.1 mN filament (Bailey Instruments, UK) following the same procedure.^36^ As for the flare, the primary area of mustard oil application will be subtracted from both hypersensitive areas such that the recorded areas represent secondary hyperalgesia/hypersensitivity.

Following mustard oil sensitisation, the MPT and HPT will be repeated using the same methods as described above. All postsensitisation tests will be performed within 5 min of mustard oil removal.

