**Figure 4 F4:**
[figure not shown]
(A) Distributions of trait variance explained by a single marker from Doehring *et al*
44 for traits included in our study and those not included. (B) Allele frequency distributions of loci associated with experimental pain in previously published cohorts, for Europeans and Colombians.

Power of a GWAS depends on the allele frequency of the SNPs through their effect on the test statistic. While the majority of GWAS studies are conducted in European-origin individuals, including the experimental pain study used to determine sample size here,^44^ our population of interest is an admixed Latin American population. Therefore, we wanted to assess the distribution of allele frequencies in Europeans versus Colombians for SNPs studied for or associated with experimental pain in various studies.^44 45^ Minor allele frequencies were obtained for all such reported SNPs from the 1000 Genomes project database^17^ for Western Europeans (from Britain (GBR), Utah residents from Northern and Western Europe (CEU), Spain (IBS), and Tuscany in Italy (TSI)) and Colombians (from Medellin in Colombia, (CLM), where this study will be performed). Allele frequency distributions for both Europeans and Colombians are shown in figure 4B. The two distributions are quite similar, with the Colombian distribution slightly more spread out. This is somewhat expected as the Colombians have on average 60% European (Spanish) ancestry.^26^ Having a well spread out distribution of allele frequencies is important in a GWAS as low-frequency alleles have lower power for a given sample and effect size.^46^ Here, the comparison to European allele frequency distribution suggests that the current Colombian cohort will have nearly equivalent power to any European-based cohort. In contrast to European-only cohorts though, our cohort will have the advantage that alleles present in other continental populations such as sub-Saharan Africans or Native Americans that are not present in Europeans would also be detectable in a GWAS, and could be followed up in replication cohorts of specific ethnicities.

The CANDELA project includes genotpyes of ~2000 patients from Medellin. We anticipate to contact and phenotype 50%–75% of these participants as well as contacting an additional 500 participants to bring the initial sample to 1500–2000.

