To facilitate better identification of associated loci, the genotype data will be imputed to approximately 10 million loci using the 1000 Genomes phase 3 imputation reference panel^52^ by first haplotype phasing using SHAPEIT2^55^ and then imputation using Impute2.^56^ Quality control of the imputed genotypes will be performed using recommended thresholds on imputation quality score, concordance metrics and proportion of high-probability calls. Details of the currently used imputation protocol for CANDELA samples^52^ are provided in online supplementary appendix 2.

GWAS studies will be conducted in Plink2^57^ to perform single-locus association studies for each trait individually, across the whole genome in an additive multivariate linear regression model.^42^ Covariates will be used in the regression to adjust for any other sources of trait variability, such as basic variables like age, sex, and BMI, and genetic PCs will be used to control for population substructure.^52 58^

The number of genetic PCs to be included in the regression depends on the sample composition, such as variation in ancestry and presence/absence of genetic outliers. It would be determined by inspecting the proportion of variance explained by each PC (displayed on a scree plot) and by checking PC scatter plots.

In addition to being used as exclusion criteria, anxiety and depression scores could be used as covariates in GWAS. The exact set of covariates to be used will be determined based on initial diagnostic analyses such as correlation analysis.

These single-locus association results, obtained as p values, will be visualised via the Manhattan plot. Commonly used p value thresholds for selecting associated loci are 5×10^−8^ for genome-wide significance and 10^−5^ for suggestive significance.^42^

An extension of this additive multivariate linear regression model, still within the single-trait single-locus setting, called the mixed linear model analysis which better controls for any cryptic relatedness or population substructure, will also be performed in GCTA.^54^

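### If the manually marked flare border depends on skin colour, the flare GWAS could return a pigmentation locus as a flare locus, because genetic PCs and the mixed model remove only the ancestry-wide part

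*Protocol article*

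**What the plan says.** **Measurement.** Under Mustard oil evoked nociceptive sensitisation, the protocol article states that "the area of the skin flare will be recorded to the nearest 0.5 cm at each spoke". Triangles between adjacent spokes are then summed and the application area subtracted. The Figure 2 legend says "the skin flare will be marked and the area calculated". No camera, perfusion imager or reflectance device is named for the flare. The strengths and limitations list adds: "Phenotypic data will be collected by a single trained examiner".

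**Sample.** The same list describes a Colombian population "with variable proportions of European, Native American and sub-Saharan African ancestry". The Sample size calculation section notes that "Colombians have on average 60% European (Spanish) ancestry". Neither place reports skin colour.

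**Analysis.** The Data analysis plan specifies "single-locus association studies for each trait individually, across the whole genome in an additive multivariate linear regression model". Covariates are introduced by example, "such as basic variables like age, sex, and BMI", and "genetic PCs will be used to control for population substructure". Anxiety and depression scores may be added, and the final covariate set is left to diagnostic analyses. A mixed linear model is also planned, to control better for cryptic relatedness and substructure. The Procedure section lists what is recorded at the visit (age, gender, self-reported ancestry, height, weight, two psychological scales); skin colour is not among these.

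**The concern.** A flare border marked on the skin depends on where the examiner can see redness end. If that visible edge shifts with skin tone, recorded flare area mixes two things: the flare and how well it shows. Skin tone is itself heritable, so alleles that change pigmentation would be associated with recorded flare without any effect on the flare.

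PCs are the usual protection in an admixed cohort, but they address a different problem. They absorb genome-wide ancestry. Among people of the same ancestry, carriers of a pigmentation allele still differ in skin colour from non-carriers, and so would still differ in recorded flare. The mixed linear model shares this limit, because relatedness and substructure are what it targets.

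At stake is the interpretation of a flare hit. The introduction hopes to reveal targets for analgesic development, and a measurement artefact taken for flare biology would point the wrong way. Any multi-trait test or admixture mapping that uses flare area could carry the same signal. The brush and pinprick areas rest on the participant's response and are not directly affected.

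**Working it through.** **Inputs from the article**
- Sample size: 50%–75% of about 2000 earlier participants, plus 500. Check: 0.50×2000+500 = 1500 and 0.75×2000+500 = 2000, which matches the stated 1500–2000.
- Thresholds: 5×10⁻⁸ (genome-wide) and 10⁻⁵ (suggestive).
- Planning range for variance explained by one marker (q²): 0.02% to 6%.

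**Inputs that are assumptions, not in the article**
- a = share of recorded-flare variance due to skin colour, given ancestry: 2% to 30%.
- b = share of skin-colour variance due to one pigmentation locus, given ancestry: 5% to 30%.

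**Step 1. Spurious effect.** q² = a × b. Examples: 5%×10% = 0.5%; 10%×10% = 1%; 10%×20% = 2%; 10%×30% = 3%.

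**Step 2. Chance that such a locus is declared significant.** A 1-df non-central chi-square test with non-centrality n·q²/(1−q²). Example: n=2000, q²=2% gives 2000×0.02/0.98 = 40.8.

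| Spurious q² | 5×10⁻⁸, n=1500 | 5×10⁻⁸, n=2000 | 10⁻⁵, n=1500 | 10⁻⁵, n=2000 |
|---|---|---|---|---|
| 0.5% | 0.3% | 1% | 5% | 11% |
| 1% | 6% | 17% | 30% | 53% |
| 2% | 53% | 83% | 87% | 98% |
| 3% | 91% | 99% | 99% | over 99% |

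For reference, 80% power at 5×10⁻⁸ needs q² of 2.57% at n=1500 and 1.94% at n=2000. The article's own power values are in Figure 3, which is not available here, so they cannot be compared. All four spurious values lie inside the article's planning range, so effect size alone would not expose the artefact.

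**Step 3. Does ancestry adjustment remove it?** Simulation, 500 runs per setting. European share was drawn from Beta(6,4), mean 0.6, with two parental groups and locus frequencies 0.95 and 0.10. True flare was independent of the locus, and the reading was shifted by skin colour with a=10%, b=20%. Exact ancestry was used as a covariate, standing in for a perfect PC.

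| Locus and adjustment | Mean chi-square, n=1500 | Mean chi-square, n=2000 |
|---|---|---|
| Pigmentation locus, unadjusted | 68 | 89 |
| Pigmentation locus, exact ancestry | 32 | 42 |
| Pigmentation locus, ancestry + skin colour | 0.9 | 1.0 |
| Equally differentiated locus without pigment effect, unadjusted | 10.0 | 12.6 |
| Same locus, exact ancestry | 1.0 | 1.0 |

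With exact ancestry adjusted, the pigmentation locus passed 5×10⁻⁸ in 58% of runs at n=1500 and 84% at n=2000, in line with the 2% row above. At a=5%, b=10%, 0% and 1% of runs passed 5×10⁻⁸, and 6% and 12% passed 10⁻⁵. Ancestry adjustment therefore does its intended job: it removes confounding at the neutral locus and reduces the signal at the pigmentation locus, but it leaves the locus-specific part. The row with skin colour assumes that colour is measured without error.

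**The case against.** - **The covariate set is open.** A reader might infer that the plan adjusts only for age, sex, BMI and PCs. It does not say so: those variables are examples, anxiety and depression scores may enter, a mixed linear model is added, and the rest awaits diagnostics. A pigmentation score would contradict no sentence of the article. This stands. However, diagnostics can select only among variables that someone has recorded or derived, and the article lists none for skin colour.
- **The premises are inferred.** The article does not state that flare is judged by eye, that skin colour varies widely on the volar forearm, or that the recorded border depends on it. The first is a fair reading of manual marking with no instrument named (Figure 2 is not shown). The second is inferred from ancestry, and the third is the condition on which the point rests.
- **The size is two assumptions multiplied.** This also stands. Flare area has an ICC of 0.610 (12 volunteers, 95% CI 0.095 to 0.869). A colour share of 10–20% of recorded variance would then be 0.10/0.610 = 16% to 0.20/0.610 = 33% of reproducible variance, with ancestry already removed, which is demanding.
- **A hit at an established pigmentation locus would be recognised.** Probably, and the article nowhere says that such a hit would be reported as sensitisation biology. But the plan does not provide for the check.

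Two apparent safeguards do not help. A stable colour bias repeats at both visits, so it raises the ICC rather than lowering it. A single examiner makes the reading consistent, but does not make it independent of skin colour.

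**Conclusion.** The point holds in conditional form. If the recorded flare border depends on skin colour, the planned PCs and mixed model remove the ancestry-wide part and leave the effect of individual pigmentation loci, so the flare GWAS could return such a locus as a flare locus. The documents do not give the size. Under the assumed spurious q² values, the chance of a genome-wide hit runs from about 1% or less (q² 0.5%) to 91–99% (q² 3%) across the planned sample sizes.

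Two stronger readings are not supported. A reader might infer that PCs do nothing against this problem; they do remove the ancestry-wide component. A reader might also infer that a false flare locus is likely; with a weak colour effect it is not, and the article has no data on how strong the effect is. The matter concerns one of the 14 measures in Table 1, plus any combined analysis that includes it.

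**What to change.** Keep the planned flare GWAS as it is, and add the following for flare area and for any multi-trait test or admixture mapping that uses it:

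1. A sensitivity run adjusted for a recorded skin-colour measure where one exists; otherwise for a score built from established pigmentation variants in the genotypes already held.
2. A re-test of each flare hit conditional on those pigmentation variants.
3. A reporting rule: a hit that lies at a pigmentation locus, or that does not survive steps 1 and 2, is flagged and not claimed as flare or sensitisation biology.

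This should be a sensitivity analysis and not the main model, because skin colour is a heritable covariate and adjusting for it in the primary analysis is debatable.

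**Cost.** A little extra analysis, with no new data needed if the genotype score is used. A locus with real effects on both pigmentation and flare would be flagged too. A score captures pigmentation incompletely, so some residual bias may remain; the simulated clean result applies only to skin colour measured without error.

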**Figure 2 F2:**
[figure not shown]
Method to determine area of flare, punctuate hyperalgesia and allodynia. (A) An acetate template is used to mark a star with eight spokes containing eight points at 1 cm increments on the volar forearm. (B) A small cotton swab soaked in 30% mustard oil is applied in the center of the star and (C) held in place with a Tegaderm for 10 min. During this time, pain scores are recorded every 30 s. (D and E) After removal of the mustard oil, the skin flare will be marked and the area calculated. (F) The area of brush-evoked and punctuate hypersensitivity will be determined with a brush and a 98.1 mN von Frey hair respectively (pictured) by testing potential hypersensitivity at each point on the eight spokes.

After mapping of the flare, the area of brush-evoked hypersensitivity will be determined with a brush (Nr 5 Senselab, Somedic, Sweden) by applying 1 cm long strokes at each of the points on the eight spokes, starting from the outside and moving towards the sensitised centre. The area of punctuate hypersensitivity will be determined with a 98.1 mN filament (Bailey Instruments, UK) following the same procedure.^36^ As for the flare, the primary area of mustard oil application will be subtracted from both hypersensitive areas such that the recorded areas represent secondary hyperalgesia/hypersensitivity.

Following mustard oil sensitisation, the MPT and HPT will be repeated using the same methods as described above. All postsensitisation tests will be performed within 5 min of mustard oil removal.

### Reliability of naïve and sensitised sensory function protocol

To determine intratester reliability, we repeated the sensory function protocol performed by the same investigator in n=12 healthy volunteers on two different occasions within 2–6 weeks. Intraclass correlation coefficients (3.1) revealed good to excellent agreement for all sensory testing variables (table 1).^38^

**Table 1 T1:** Intratester reliability of sensory function protocol

	Intraclass correlation coefficients	95% CI	P value
CDT	0.728	0.277 to 0.914	0.003
WDT	0.764	0.351 to 0.927	<0.0001
TSL	0.638	0.161 to 0.878	0.005
HPT	0.752	0.339 to 0.922	0.002
MPT	0.928	0.767 to 0.979	<0.0001
WUR	0.634	0.113 to 0.880	0.012
VDT	0.956	0.860 to 0.987	<0.0001
PPT	0.734	0.305 to 0.915	0.002
VAS	0.893	0.667 to 0.970	<0.0001
Flare area	0.610	0.095 to 0.869	0.015
Brush-evoked allodynia	0.756	0.365 to 0.922	0.001
Punctuate hyperalgesia	0.615	0.094 to 0.871	0.013
Postsensitisation MPT	0.941	0.808 to 0.983	<0.0001
Postsensitisation HPT	0.758	0.339 to 0.924	0.002

CDT, cold detection threshold; HPT, heat pain threshold; MPT, mechanical pain threshold; PPT, pressure pain threshold; TSL, thermal sensory limen; VDT, vibration detection threshold; VAS, Visual Analogue Scale; WDT, warm detection threshold; WUR, wind-up ratio.

### Genotyping

Each participant will donate blood or saliva (Oragene OG-500, Genotek, Canada) for DNA extraction. DNA samples will be genotyped on the Illumina HumanOmniExpress chip containing ~700 000 markers. In volunteers who already participated in the CANDELA GWAS,^39^ genotype data from blood samples genotyped on the same chip are already available and will be reused.

Whole-genome genotype data from the Illumina array will undergo quality control^40^ to exclude any markers or samples that fail stringent thresholds. Quality metrics provided by the genotype calling algorithm in the Illumina GenomeStudio software,^41^ such as the GenTrain score, cluster separation score, and excess heterozygosity rates will be used to filter poorly genotyped SNPs. Subsequent SNP-level and sample-level quality control thresholds such as missingness will be applied. Sex mismatch between records and genetic data of X and Y chromosomes will be checked. Only samples and SNPs that pass all criteria will be retained for analysis. Details of the currently used quality control protocol for CANDELA genotyped samples are provided in online supplementary appendix 2.

10.1136/bmjopen-2018-025530.supp2Supplementary data

### Statistical analysis

#### Sample size calculation

The power for GWAS of experimental pain phenotypes for varying sample and effect sizes was estimated following the formulae described in Visscher *et al*.^42^ Estimated power is shown for a range of effect sizes for experimental pain phenotypes taken from existing experimental pain studies. The statistical software R V.3.4.1^43^ was used to perform the calculations and produce the figures. The codes are published on https://github.com/[name]/gwas-power.

In whole-genome SNP-based GWAS studies, the association analysis is usually conducted with a multivariate linear regression model, where the trait values are regressed onto an SNP genotype (with additive coding) and other covariates which commonly include age, gender, BMI and genetic principal components (PCs). The p value threshold^39 42^ for genome-wide significant associations is commonly 5×10^−8^, while the threshold for a suggestive significant association is commonly 10^−5^. Formulae to calculate power in GWAS with genome-wide and suggestive significance thresholds are presented in online supplementary appendix 3, and power calculated for the current GWAS setting is shown in figure 3.

10.1136/bmjopen-2018-025530.supp3Supplementary data

**Figure 3 F3:**
[figure not shown]
Estimated power (in percentage) under the standard genome-wide association studies (GWAS) settings of using whole-genome genotyping data. (A) Estimated power (in percentage) as a heatmap, setting the significance threshold at 5×10^−8^, the commonly used threshold for genome-wide significance in GWAS studies. (B) Estimated power with the significance threshold set at 10^−5^, the commonly used threshold for suggestive significance. In panels A-B, the x-axis denotes a range of sample sizes (n) in a GWAS, the y-axis represents the proportion of trait variance (q^2^) explained by a marker. Power of detecting the marker at a specific (n, q^2^) combination is represented by a colour gradient. Contour lines for power at 10% intervals are also shown. Panels C-D shows power curves for the expected sample sizes for this study. (C) Expected power at genome-wide and suggestive significance thresholds for a sample size of n=1500. (D) Estimated power for a sample size of n=2000. In Panels C-D, the x-axis denotes the proportion of trait variance (q^2^) explained by a marker, and y-axis represents estimated power (in percentage). The two curves correspond to the two commonly used GWAS thresholds. In each panel, the point for 80% power is indicated with a green triangle, so that the necessary parameter configurations can be read from the graph. In panels A-B, the contour corresponding to 80% power is also marked in green.

Figure 3A shows estimated power (in percentage) as a heatmap under the standard GWAS settings of using whole-genome genotyping data and a p value significance threshold of 5×10^−8^. Sample size (n) varies from 100 to 5000, while the proportion of trait variance explained by the marker (q^2^, in percentage) varies from 0.01% to 6%. As sample size increases, power increases quickly for a range of trait variance values to reach 100%.

Figure 3B shows estimated power (in percentage) under the same settings but a suggestive p value significance threshold of 10^−5^. As expected, power is higher at similar sample and effect sizes for this less stringent threshold.

Simplified power estimates are shown as power curves in figure 3C,D for the expected sample sizes for this study. Figure 3C shows expected power at genome-wide and suggestive significance thresholds for a sample size of n=1500 at varying effect sizes, while figure 3D shows estimated power for a sample size of n=2000.

The range of trait variance has been taken from Doehring *et al*,^44^ which provides estimates for the proportion of trait variance explained by an SNP for several experimental pain phenotypes and multiple markers. The values ranged from 0.02% to 6%. Some of the traits were the same as the traits investigated here, while some other traits were different. Nevertheless, the distributions of trait variance for the two groups of traits are very similar, as seen in figure 4A.

